
## II. Background and Significance

Asthma morbidity and mortality. Asthma is a chronic inflammatory disease of the lungs. In the United States, asthma affects approximately 15 million persons, including 5 million children 1. It is estimated that people in the United States with asthma collectively experience 100 million days of restricted activity, nearly 500,000 hospitalizations and approximately 5,000 deaths annually 29. In addition, patients with asthma report significantly more physically unhealthy days, more mentally unhealthy days and more days with activity limitation than those without asthma 30. Despite widespread availability of consensus guidelines from the National Asthma Education and Prevention Program, many patients with asthma have poor asthma control and do not get care consistent with the guidelines 26. For example, Mularski and colleagues recently published a study showing that adult asthma patients received 53.5% of recommended care processes 31. Progress has been made with improving the use of controller medications in the United States, however. In a study of the National Ambulatory Medical Care Survey, Ma and colleagues observed that inhaled corticosteroid use in asthma increased from 25% in 1992 to 42% in 2002 8. Similarly, among a national group of health plans, controller medication use was up to over 80% in 2005, versus only 58% in 1997 7,8. Despite this increase in availability of controller medicines, such as inhaled corticosteroids (e.g., beclomethasone) and long-acting beta-2 agonists (e.g., salmeterol) more than half of adults with asthma do not have their symptoms controlled 5,6. For example, Schatz and colleagues noted, among a random sample of asthmatic patients with health insurance, 51.7% had an Asthma Control Test (ACT) score < 20, a level at which the 2007 NAEPP Guidelines suggest is consistent with uncontrolled asthma 5,26. Similarly, Vollmer and colleagues reported that 52% of 5181 adults in a large managed care organization had at least one asthma control problem, according to the Asthma Quality of Life Questionnaire (AQLQ) 6. Carlton and colleagues reported that nearly 75% of 25,163 adults with asthma had at least one symptom consistent with poor control 32. A major reason for this lack of asthma control is that many patients whose asthma is not controlled are taking one, rather than multiple, controller medications, which are suggested in the 2007 NAEPP Guidelines 26,32. This suggests that focusing solely on the availability of controller medication use may not be enough to improve asthma control in the United States. Many other recommendations, however, are not being followed. The 2003 National Asthma Study, however, observed that fewer than 70% of adults with asthma were taught to recognize early symptoms of asthma, fewer than 50% were instructed to change their environment and fewer than 30% received an asthma action plan 9. Other investigators have observed similar patterns 10,31,33. In summary, this suggests that there are many opportunities to improve the care and control of asthma, by more rigorously applying clinical practice guidelines. This also suggests the need to modify the main outcome measure in the study, from controller medication availability, to asthma control. Many patients have at least one controller medication and still have poor asthma control.

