### Inclusion/exclusion criteria

In order to be eligible for the study, all patients must:

1) be between 21 and 60 years of age

2) have evidence of physician-diagnosed asthma, including at least one documented asthma-related medical encounter in the past year AND at least 3 months of asthma-related medications in the past year.

3) have self-reported asthma, based on questions from the National Asthma Survey from the Centers for Disease Control (CDC) 9.

4) speak and read English fluently

5) have access to the Internet at home or at work

6) not have a history of more than 20 pack-years of cigarette smoking.

7) be enrolled in a Highmark health plan .

8) not currently pregnant

No children will be included in the proposed. While this work is important to do, we believe that the costs of running two parallel studies (two entirely different websites and recruitment strategies) would not outweigh the additional knowledge learned, at least at this time. As the studies that informed the creation of the intervention only included adults 24,27,28,90, a significant amount of development work would need to be done that would likely result in very different interventions for adults and children. If this approach is successful, future studies could extend these findings by developing interactive websites for children, who, on average, have higher rates of Internet access 83, or for their parents to use.

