Controller to reliever ratio: There are generally two types of medicines for asthma; those used for quick relief of asthma symptoms (“relievers”), and those that are used daily to prevent asthma symptoms (“controllers”). Using a controller medication is the first step in managing persistent asthma, according to the treatment algorithm (page 343) on the 2007 NAEPP Guidelines 26, and has served as a main outcome measure in many quality improvement studies 66-68,104. By using more controller medicines, therefore, the number of reliever medicines tends to go down 105. The ratio of controller/reliever canisters is strongly predictive of future emergency department visits and, as such, has been used as a measure of asthma control and quality of care 105-107. As the intervention is designed to help individuals receive a controller medicine and, for those whose asthma is not controlled, often a second controller medicine, the controller to reliever ratio should be sensitive measure of the effects of the intervention. We will use standard ways to express this variable, which will be calculated as the ratio of the number of controller medications (i.e., inhaled corticosteroid) dispensed during the study year divided by the sum of the number of controller medications dispensed plus the number of canisters of inhaled relievers (e.g., short-acting beta-2-agonists) dispensed during the study year. This ratio ranges from 0 (no controller medications) to 1.0 (no reliever medications) 105-108. Grymonpre and colleagues observed that the concordance between claims data on medication acquisition and pill counts was between 79% and 88%, which were both highly significant 109. This data will be captured in the electronic claims data from Highmark, as none of the medicines are inexpensive, so patients should find it less expensive to use their prescription drug coverage through Highmark than to pay out of pocket. Similar methods are used by the National Committee for Quality Assurance to estimate the quality of asthma care in over 500 health plans nationally 7.

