Medication Adherence: The intervention, in some cases, will suggest that patients discuss medication adherence with their provider. This is based on the recommendation (page 336) that “before increasing therapy, however, the clinician should review the patient’s inhaler technique and adherence to therapy” 26. We will measure medication adherence to all asthma controller medications, such as inhaled corticosteroids and long-acting beta-2 agonists, using health care claims for asthma-related medications from Highmark. Health care claims have been shown to be a valid and reliable way to assess medication adherence 109. Our measure of adherence will be the Medication Possession Ratio (MPR), a commonly used measure of adherence, that is highly correlated with other measures of adherence and predictive of asthma exacerbations 111-116. The MPR measures the percentage of doses available to the patient during a specific time period. [name] has experience, through multiple clinical trials for asthma, in measuring adherence to asthma medications and will oversee analysis of medication adherence data 117,118 . Though medication adherence is not a main focus of the intervention, we hypothesize that, by encouraging patients to discuss medication adherence-related issues with their provider, patients in the IC will have higher rates of adherence to their controller medications than subjects in the CC.

**Moderating variables**: For our purposes, moderating variables are those that the intervention will not seek to modify, yet may lead to a differential response to the intervention.

Demographics: Age, gender, race, ethnicity, educational achievement, marital status and household income will be measured, using standardized instruments such as those from the Behavioral Risk Factor Surveillance System 119,120. These variables have been shown to be related to asthma prevalence, asthma quality of care and asthma-related quality of life 121-123. We will assess these variables at baseline and use the data to assess whether demographic variables, such as household income, moderate the effect of the intervention on inhaled corticosteroid use or asthma control.

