### 7. Statistics and sample size justification

Sample size considerations focus on the primary hypothesis posited in the Specific Aims section. The major research goal is to determine the efficacy of having patients use the asthma module of the interactive website, for a period of 12 months, for improving asthma control. The primary outcome will be asthma control, based on the Asthma Control Test (ACT), a valid and reliable 5-question self-report measure of asthma control. 98-100. We chose to power the study based on asthma control, as it is a powerful predictor of emergency department visits, activity limitations and missing days of work due to asthma 6,100,130, and it is a central goal in both Healthy People 2010 as well as in the 2007 NAEPP Guidelines 26,131. We chose not to power the study on improving the use of controller medications, such as inhaled corticosteroid use, as the rates of use of these medications has increased greatly over the past decade, which would lead to a ceiling effect 7. Despite the broad use of these controller medications, however, asthma control rates are still in the 50% range, so we will not suffer from such a ceiling effect 5. Our estimated baseline rate of 55% is based on two studies of asthma control in similar groups of insured patients that both showed asthma control rates in the 50% range 5,6. For example, Schatz and colleagues observed that 48.4% of 570 insured adults with asthma had an Asthma Control Test (ACT) score of less than 20, the same measure of asthma control that we are using in the current study 5. Vollmer and colleagues reported that 48% of 5,181 insured adults with asthma reported good asthma control, using a slightly different measure of asthma control, the Asthma Quality of Life Questionnaire 6. We expect a slightly higher baseline control rate, as patients who volunteer for clinical trials tend to be healthier than those who do not 132. This expected effect size is based on a meta-analysis by Stone and colleagues that examined the efficacy of reminders, given to patients, on rates of adult immunization and cancer screening services 16. Patient reminders, similar to what we plan to use in the current study, significantly increased immunizations (odds ratio, OR=2.5), mammography utilization (OR=2.3), cervical cytology screening (OR=1.7) and colon cancer screening (OR=2.8). These effect sizes are consistent with reviews by other investigators 23,50,133. In the current study, we will be powered to detect an effect size that translates to a relative risk of 1.3 (0.70 /0.55) and odds ratio of 1.9. We chose this conservative effect size to address the fact that we are not examining a process of care but an outcome of care. While we expect the intervention to lead to increases in the number of controller medications used, additional medications do not always help patients. Also, we need to be sensitive to the possible differences in efficacy between interventions to increase adult preventive services (e.g., pap testing) and studies such as ours that seek to change chronic disease management practices. We considered powering on a numerical change in the Asthma Control Test (ACT), our main outcome measure, but chose not to do this as there is less consensus about what represents a meaningful change in the ACT than there is about what represents appropriate asthma control 5,98. We will, however, analyze changes in the ACT as a continuous variable, in our secondary analyses. Formulas based on the chi-square test were used to derive sample size calculations from the following assumptions. We assume a type I error rate (alpha) of 5% (0.05), 80% (0.80) power, and a two-tailed test, which allows us to detect significant differences in either direction. We expect a 12-month retention rate of 80%, although we believe that our procedures will substantially minimize the likelihood of attrition. We considered randomizing providers but felt that, given the number of providers in the two geographical areas, it was very unlikely that a physician would have more than one subject enrolled in the study. We will, however, track the name of the asthma care provider, so that we can include this variable in a sensitivity analysis, to be certain that adding this variable does not change the conclusions of the data analyses. In order to achieve 80% power to detect a difference of 70% vs. 55% between intervention and control group, we will need to randomize 408 patients into the two conditions at baseline. This assumes that no more than 20% are lost to follow-up at 12 months, leaving no fewer than 326 subjects available for analysis at the end of the study. We do concede, however, that smaller differences in asthma control may be clinically important, particularly on a population level. To power the study on a 10% difference in asthma control, however, we would have needed to recruit 940 subjects, which we felt would unnecessarily increase the cost and complexity of the study.

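### Controller adherence (MPR) is compared between arms without fixing before randomisation who contributes, although the intervention itself starts and adds controllers

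*Protocol*

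**What the plan says.** Protocol section 6, under Medication Adherence, names the instrument: "Our measure of adherence will be the Medication Possession Ratio (MPR), a commonly used measure of adherence". It covers every controller ("We will measure medication adherence to all asthma controller medications, such as inhaled corticosteroids and long-acting beta-2 agonists") and is described only in general terms: "The MPR measures the percentage of doses available to the patient during a specific time period". The hypothesis is stated over whole arms: "patients in the IC will have higher rates of adherence to their controller medications than subjects in the CC". Specific Aims and the Secondary analyses paragraph of section 7 repeat it as a secondary hypothesis. Section 7 assigns it a linear mixed-effects model. Section 6 also lists adherence among the mediators, which section 7 tests by the Baron and Kenny steps.

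Three other places bear on who has an MPR.

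- The medication criterion for entry is "at least 3 months of asthma-related medications in the past year", which a reliever can satisfy.
- Section 6, under Controller to reliever ratio, says "the intervention is designed to help individuals receive a controller medicine and, for those whose asthma is not controlled, often a second controller medicine".
- Section 7 adds "we expect the intervention to lead to increases in the number of controller medications used".

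No restriction to subjects already on a controller at baseline is stated.

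**The concern.** Having a controller, and how many, is an outcome of the intervention. An MPR needs prescribed controller doses in its denominator, so a subject never dispensed one has no value. The Protocol does not say this; it follows from how the ratio works. IC subjects who start a controller because of the website enter the comparison, while their CC counterparts, who did not start, are absent. The contrast is then not between the groups that were randomised.

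A second controller acts differently. It does not select subjects, but it changes the mix of drugs behind a subject's MPR, and does so more often in IC.

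An adherence difference of either sign could therefore arise with no change in how anyone refills. The same difference would feed the mediation analysis, whose second step asks for an association between treatment and mediator.

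**Working it through.** The Protocol gives no planning figure for adherence. Its 408 randomised and 326 evaluable (408 × 0.80 = 326) concern the ACT. They are used here only for scale: 163 per arm.

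**Inputs.** Baseline controller use c = 0.80, from section II: "controller medication use was up to over 80% in 2005, versus only 58% in 1997"; the older 58% is the low case. Everything else is assumed, since the Protocol gives no MPR values: existing users' MPR 0.60 in both arms, SD 0.30, refilling unchanged. A further share a of IC subjects starts a first controller, with MPR m.

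**New starters, MPR among dispensed subjects only.** IC mean = (c × 0.60 + a × m)/(c + a); CC mean = 0.60; so the difference is a(m − 0.60)/(c + a).

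| c | a | m = 0.30 | m = 0.60 | m = 0.90 |
|---|---|---|---|---|
| 0.80 | 0.05 | -0.018 | 0 | +0.018 |
| 0.80 | 0.10 | -0.033 | 0 | +0.033 |
| 0.80 | 0.15 | -0.047 | 0 | +0.047 |
| 0.58 | 0.15 | -0.062 | 0 | +0.062 |

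Example: (0.80 × 0.60 + 0.15 × 0.30)/0.95 = 0.553, and 0.553 − 0.600 = -0.047. The sign depends only on whether starters have a lower or higher MPR than existing users.

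**Against sampling error.** SE = 0.30 × √(1/(163(c + a)) + 1/(163c)). For c = 0.80, a = 0.10 this is 0.30 × √(1/147 + 1/130) = 0.036, so a shift of 0.033 is just under one standard error. A nominal 5% two-sided test would reject in about 15% of trials there, 26% at a = 0.15, and 32% at c = 0.58, a = 0.15.

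**Scoring subjects without a controller as 0.** The difference becomes a × m: from 0.05 × 0.30 = +0.015 to 0.15 × 0.90 = +0.135. It always favours IC, because the measure then counts initiation.

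**Second controllers.** Let a share s of IC users (0.10 to 0.40) add a drug with MPR m2 (0.30 to 0.90).

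- Averaging over drugs: s(m2 − 0.60)/2. At s = 0.40 this runs from -0.06 to +0.06, and is 0 if m2 = 0.60.
- Summing supply, capped at 1: s(min(1, 0.60 + m2) − 0.60). From 0.10 × 0.30 = +0.03 to 0.40 × 0.40 = +0.16, always favouring IC.

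**Set fixed before randomisation.** Among subjects with a controller at baseline, MPR on the baseline drug(s) is 0.60 in both arms under the same assumptions: a difference of 0.

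**The case against.** The strongest reply is that the analysis set, the MPR period, the treatment of subjects with no fill and the rule for several drugs usually belong in the SAP, which is not shown, and that each figure above needs one of those rules to be set unfavourably. Much of this stands. If a starter's period begins at first fill and that subject refills at 0.60, the new-starter shift is zero. If expected doses are counted for both drugs and both are filled at the same rate, the second-controller shift is zero too.

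The reliever-only group may also be small. Section 4 screens for persistent asthma by HEDIS criteria, section 6 calls a controller the first step in managing persistent asthma, and section 7 expects a ceiling in controller use. The documents give no figure for the size of that group. Section 6 adds that adherence is not a main focus of the intervention.

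What does not stand is that derivation rules alone would settle it. Dropping subjects without a controller leaves groups chosen after randomisation; scoring them 0 turns adherence into initiation. An MPR for someone never prescribed a controller is undefined rather than missing, so the multiple imputation in section 7 does not supply it. The hypothesis in sections 6 and 7 covers all patients in each arm, and that is what has to be narrowed.

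A reader might go further and infer a large built-in advantage for IC. If 25% of IC users added a second drug and its supply were summed without its doses or a cap, those users' MPR would be 1.20 and the mean 0.75 × 0.60 + 0.25 × 1.20 = 0.75, a 15-point gain. Nothing in the Protocol prescribes that calculation. Capped at 1 it is 0.25 × 0.40 = 10 points, and with doses counted for both drugs it is zero.

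**Conclusion.** The point holds as a design weakness of a secondary outcome and mediator. The adherence contrast is conditional on controller receipt, which the intervention is built to change, and no pre-randomisation restriction is stated. The likely distortion from new starters is modest: about -0.05 to +0.05 at 80% baseline controller use, and about -0.06 to +0.06 at 58%. Second controllers could add -0.06 to +0.16, depending on the combining rule. All of this rests on the assumed MPR of 0.60, the range 0.30 to 0.90 for added drugs, and the assumed shares starting or adding a drug.

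A reader might conclude that the adherence result could neither support nor refute the hypothesis. The documents do not support that: the shift may be zero under reasonable rules, the group newly starting a controller may be small, and a shift of 0.033 is within one standard error at the assumed SD. The ACT primary comparison is unaffected.

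**What to change.** In section 6 (Medication Adherence) and section 7 (Secondary analyses), define the adherence set as randomised subjects with a controller dispensed in the pre-enrolment claims. Section 5 already obtains two years of these, and section 7 already uses baseline controller use as a variable; the look-back window should be named. Compare MPR on the controller drug(s) or class in use at baseline, from randomisation to month 12, capped at 100%. Report controller initiation or exposure, with 0 for none, separately in all randomised subjects and not under the name of adherence.

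Days covered by at least one controller is a tempting substitute but keeps part of the problem. With 0.60 coverage per drug and independent gaps (an assumption), two drugs cover 1 − 0.4 × 0.4 = 0.84 of days. If 25% of IC users add one, the IC mean is 0.75 × 0.60 + 0.25 × 0.84 = 0.66 against 0.60, with refilling of each drug unchanged.

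The cost is Protocol wording and derived variables from claims already planned. The adherence set becomes somewhat smaller (about 80% of subjects on the section II figure), adherence to newly added drugs is only described, and a rule is needed for switches within a class.

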### 7. Statistics and sample size justification

Sample size considerations focus on the primary hypothesis posited in the Specific Aims section. The major research goal is to determine the efficacy of having patients use the asthma module of the interactive website, for a period of 12 months, for improving asthma control. The primary outcome will be asthma control, based on the Asthma Control Test (ACT), a valid and reliable 5-question self-report measure of asthma control. 98-100. We chose to power the study based on asthma control, as it is a powerful predictor of emergency department visits, activity limitations and missing days of work due to asthma 6,100,130, and it is a central goal in both Healthy People 2010 as well as in the 2007 NAEPP Guidelines 26,131. We chose not to power the study on improving the use of controller medications, such as inhaled corticosteroid use, as the rates of use of these medications has increased greatly over the past decade, which would lead to a ceiling effect 7. Despite the broad use of these controller medications, however, asthma control rates are still in the 50% range, so we will not suffer from such a ceiling effect 5. Our estimated baseline rate of 55% is based on two studies of asthma control in similar groups of insured patients that both showed asthma control rates in the 50% range 5,6. For example, Schatz and colleagues observed that 48.4% of 570 insured adults with asthma had an Asthma Control Test (ACT) score of less than 20, the same measure of asthma control that we are using in the current study 5. Vollmer and colleagues reported that 48% of 5,181 insured adults with asthma reported good asthma control, using a slightly different measure of asthma control, the Asthma Quality of Life Questionnaire 6. We expect a slightly higher baseline control rate, as patients who volunteer for clinical trials tend to be healthier than those who do not 132. This expected effect size is based on a meta-analysis by Stone and colleagues that examined the efficacy of reminders, given to patients, on rates of adult immunization and cancer screening services 16. Patient reminders, similar to what we plan to use in the current study, significantly increased immunizations (odds ratio, OR=2.5), mammography utilization (OR=2.3), cervical cytology screening (OR=1.7) and colon cancer screening (OR=2.8). These effect sizes are consistent with reviews by other investigators 23,50,133. In the current study, we will be powered to detect an effect size that translates to a relative risk of 1.3 (0.70 /0.55) and odds ratio of 1.9. We chose this conservative effect size to address the fact that we are not examining a process of care but an outcome of care. While we expect the intervention to lead to increases in the number of controller medications used, additional medications do not always help patients. Also, we need to be sensitive to the possible differences in efficacy between interventions to increase adult preventive services (e.g., pap testing) and studies such as ours that seek to change chronic disease management practices. We considered powering on a numerical change in the Asthma Control Test (ACT), our main outcome measure, but chose not to do this as there is less consensus about what represents a meaningful change in the ACT than there is about what represents appropriate asthma control 5,98. We will, however, analyze changes in the ACT as a continuous variable, in our secondary analyses. Formulas based on the chi-square test were used to derive sample size calculations from the following assumptions. We assume a type I error rate (alpha) of 5% (0.05), 80% (0.80) power, and a two-tailed test, which allows us to detect significant differences in either direction. We expect a 12-month retention rate of 80%, although we believe that our procedures will substantially minimize the likelihood of attrition. We considered randomizing providers but felt that, given the number of providers in the two geographical areas, it was very unlikely that a physician would have more than one subject enrolled in the study. We will, however, track the name of the asthma care provider, so that we can include this variable in a sensitivity analysis, to be certain that adding this variable does not change the conclusions of the data analyses. In order to achieve 80% power to detect a difference of 70% vs. 55% between intervention and control group, we will need to randomize 408 patients into the two conditions at baseline. This assumes that no more than 20% are lost to follow-up at 12 months, leaving no fewer than 326 subjects available for analysis at the end of the study. We do concede, however, that smaller differences in asthma control may be clinically important, particularly on a population level. To power the study on a 10% difference in asthma control, however, we would have needed to recruit 940 subjects, which we felt would unnecessarily increase the cost and complexity of the study.

Preliminary data analysis plan: All analyses will be conducted using SAS Version 9. Initially, descriptive statistics such as the minimum, maximum, range, median, quartiles, mean, and standard deviation for each continuous variable and frequencies and percentages for each categorical variable will be used to summarize all variables as well as detect outliers, data entry mistakes, and missing values. These descriptives will be used to “clean” the data prior to analysis. Exploratory graphical techniques will be used to further examine these data. The normality of the distribution of mediators of interest, both in their original and transformed state (if necessary), will be examined with a normal probability plot when applicable. Longitudinal plots will be used to identify trends over time that are both population- and individually-based.

Differential dropout and attrition: Initially, the two randomized groups will be compared on important demographic and other baseline variables to ensure successful randomization. If it is determined that the groups, by chance, are significantly different on some measures, we will include those theoretically meaningful confounders as covariates in subsequent analyses. T-tests, ANOVA, and/or chi-square tests of independence comparing those who complete the study with those lost to follow-up will be performed on baseline demographic variables, asthma control, asthma-related quality of life, and baseline use of controller medications to identify potential differential dropout. These comparisons ensure equality of intervention and comparison groups after accounting for study attrition. For the primary outcome, we will apply intention to treat (ITT) principles with all available data included in the first set of analyses 134. Second, subjects lost to follow-up will be conservatively assumed to have not changed their level of asthma control between baseline and 12 months. Similar findings between both approaches would increase confidence in the results overall.

Missing data: For exploratory analyses, if the combined rate of missingness on predictor variables is less than 5%, the missing data will not be replaced. In the event of unanticipated higher levels of missing data, we need to examine the nature of the missing values. If it is believed that variations in attrition can be explained by observed variables (e.g. if those who are observed to have poorer asthma control at baseline are more likely to drop out), this corresponds to the missing at random (MAR) assumption and the models as we have specified them will give valid inferences because they are likelihood-based 135, and no special adjustments are necessary. If instead we believe that some of the variability in attrition might further be explained by variables not observed, then we will employ multiple imputation 136 (i.e., using PROC MI in SAS) which have been shown to yield estimates that are comparable to those that would be obtained if the data were all present. Because such imputations are necessarily based on assumptions that cannot be verified, we will carry out sensitivity analyses to investigate violations of these assumptions.

Analysis of main outcome: Data analysis will focus on the primary hypotheses that significantly more subjects in the IC will have their asthma controlled, an Asthma Control Test (ACT) score of ≥ 20, than subjects in the CC. This dichotomized version of the ACT at 12 months is the primary outcome. We considered powering on a numerical change in the Asthma Control Test (ACT), our main outcome measure, but chose not to do this as there is less consensus about what represents a meaningful change in the ACT than there is about what represents appropriate asthma control 5,98. Logistic regression will be used to analyze asthma control at 12 months. Logistic regression allows for inclusion of the two dichotomous strata. Also, it is possible that the groups may have differences at baseline in potential confounders (e.g. socio-economic status, asthma symptoms) that may contribute to group differences in the 12 month event rate between the two conditions. Logistic regression permits inclusion of these potential confounders as covariates. Additionally, as the ACT is measured every 3 months, the logistic regression model can be extended using the generalized estimating equations (GEE) approach of Zeger and Liang (1986) with a logit link so that the repeated measures on each subject can be included in the analyses 137. Thus, asthma control can be examined at any of the preceding time points as well. Tests of the primary hypotheses about intervention effects will be formulated directly in terms of the main effect of intervention. We will also assign a create variables for physicians’ practices, so that physicians who practice together will be given the same variable number. In our analyses we first perform intent-to-treat (ITT) analyses and then will perform analysis including physician- and practice-level variables, while accounting for clustering.

Secondary analyses: The secondary hypotheses, taken from the Specific Aims, are that subjects in the IC will have fewer asthma-related emergency department visits, greater gains in their asthma-related quality of life, greater increases in their controller-to-reliever medication ratio, greater satisfaction with asthma treatment and greater adherence to their asthma controller medications, after 12 months, than will patients in the CC. Statistical analyses for these hypotheses will follow the analytic plan as described for the primary outcomes. Secondary outcomes that are dichotomous (e.g. improved asthma-related quality of life) will be fit using the GEE approach with a logit link, which extends the logistic regression model, as described previously. Outcomes that are continuous (e.g. asthma control, adherence) will be analyzed using the linear mixed-effects model developed by Laird and Ware (1982) which extends linear regression to allow for repeated measurements. Ordinal measures will be estimated as a cumulative odds regression model 138 after satisfying the assumptions of proportionality between levels of the outcome and the explanatory variables. When this assumption cannot be satisfied, nonproportional models, such as logistic regressions between adjacent categories, will be examined.

Analyses of mediating and moderating processes: The analytic procedures outlined provide a convenient way of identifying effect modifiers and confounders, while modeling the underlying relationship of interest. As noted in the analytic plan for the primary outcome, the analysis of moderators will be undertaken by creating interaction terms between treatment and covariates of interest, such as asthma-related quality of life 139, health literacy and socio-demographic characteristics. We will also examine the effects of treatment fidelity and intervention dosage (e.g. number of visits to web site, total time spent on web site) as potential moderators of intervention efficacy. Mediational analyses will be conducted in the form proposed by Baron and Kenny 140. Briefly, this entails four steps in which it is demonstrated that there is: a) a significant association between the independent variable and the dependent variable; b) a significant association between the independent variable and the mediators; c) a significant association between the mediator and outcome; and d) a meditational effect is argued to occur when a significant decrease in the relation between the independent (e.g. treatment) and dependent (e.g. asthma control) variables upon the forced entry of the proposed mediators into the model at the final step. We will examine each mediator separately, as joint estimation makes estimation and interpretation of the effect of each potentially mediating variable problematic. Data for these analyses will be obtained from online surveys, date stamps from the interactive website and from the timing of physician visits from chart reviews. For example, we can test whether use of the interactive website influences use of other asthma controller medications (e.g., salmeterol). However, we will also explore various temporal combinations between the exogenous (treatment), endogenous mediators (asthma specialist visits) and outcomes and we will pay particular attention to the temporal ordering of key events and measurement periods.

Ancillary analyses: We plan a detailed tracking and analysis of the delivery and receipt of the intervention components in both the IC and CC conditions. Intervention components will be collected and analyzed using an intervention checklist administered to the subject after the first physician visit, as well as passive monitoring of website usage for all subjects. An implementation index will be calculated for all subjects based on which intervention components each subject was exposed to and for what duration/intensity. This continuous measure will be utilized as a covariate in outcome analyses. Further, we plan to explore the receipt of each treatment component and identify subject characteristics (e.g. age, gender) that are associated with receipt/utilization of a given component. This analytic strategy is particularly useful for gauging utilization of the website. First, we will use descriptive methods to examine total time spent on the website, number of pages viewed and number of times the computer tailored feedback was viewed, all of which can be correlated in relation to the timing of doctor visits, as well as asthma control. Next, we will examine website usage as an outcome variable to characterize which types of patients are more likely to utilize the website. Finally, we plan to examine utilization of the website as predictor of the main study outcomes. These analyses will also be important to provide: a) feedback for website design and management; b) internal validity checks on utilization, which represents dosage and exposure to the intervention; and c) a computation of the effect of dosage, which will be used as a covariate in the prediction of outcomes on the hypothesis that greater utilization of the internet will increase the likelihood of positive outcomes in key intervention indicators, such as use of asthma controller medications. These analyses will permit conclusions regarding the degree to which patient characteristics influence utilization of the website as well as whether the time spent viewing and content of pages viewed influences study outcomes.

